### Screening

For conduct of the screening, a trained clinical psychologist administers the Structured Clinical Interview for DSM-V (SKID-5-CV) after the participant gives informed consent. Further, participants are asked for a urine sample to apply a drug test and, if applicable, a pregnancy test.

### Baseline assessment

Following the group assignment, participants complete a baseline assessment that begins with a screening session, which determines whether the participants qualify for this study, and includes questionnaires, a neuropsychological assessment and an fMRI session. The questionnaires are focused on demographics, alcohol use, current medication and clinical symptoms. For a comprehensive list of the questionnaires used, please see Table 1. During the neuropsychological assessment, participants perform a dot probe task with alcohol stimuli to assess attentional bias for alcohol [53] and a dimensional card sorting task to measure executive functioning [22]. Then, participants are instructed to set three goals for the intervention. The fMRI session consists of a cue-reactivity paradigm to reflect incentive salience [47], a delay discounting task [21] investigating impulsivity [41] and a stop signal task to assess motor inhibition [23]. Participants who receive MBRP additionally receive an introduction to the program and a short exercise in mindfulness.

**Table 1 Tab1:** Chart of measurements implemented in the study

**Measurement**	S01	MRI 1/baseline	MBRP	MRI 2	MRI 3	MRI 4	MRI5/ Post	FU1/2	FU3
Consent Form for the Study	X								
Sociodemographic Information		X							
Structured Clinical Interview (SKID – I)	X								
Drinking Assessment Interview (Form90)		X							
Urine Sample (Pregnancy & Drugs)	X								
Breath Alcohol Test									X
Current Medication	X								
Current Drug Use	X							X	X
MBRP Confidence Scale				X	X	X			X
MBRP Fidelity Scale			X						
Clinical & Personality Questionnaires	S01	MRI 1/ baseline		MRI 2	MRI 3	MRI 4	MRI5/ Post	FU1/2	FU3
General Depression Scale (Allgemeine Depressionsskala)		X							
Positive and Negative Affect Scale (PANAS)		X							
Perceived Stress Scale (PSS)		X							
Behavioral Inhibition/Approach System (BIS/BAS)		X							
Baratt Impulsiveness Scale (BIS-15)		X							
Fagerstrom Test of Nicotine Dependence (FTND)		X							
Goal Attainment Scaling		X							X
Sensory Inventory		X							
Alcohol-Related Questionnaires	S01	MRI 1/ Baseline		MRI 2	MRI 3	MRI 4	MRI5/ Post	FU1/2	FU3
Quick Drinking Assessment Interview (Form 90)								X	X
Alcohol Dependence Scale (ADS)		X							
Alcohol Abstinence Self-Efficacy Scale (AASE)		X							X
German Inventory of Drinking Situations (DITS-40)		X							
Obsessive Compulsive Drinking Scale (OCDS)		X							X
Alcohol Urge Questionnaire (AUQ)		X							X
Craving-Automatized-Scale-Alcohol (CASA)		X							X
Neuropsychological Tests	S01	MRI 1/ Baseline		MRI 2	MRI 3	MRI 4	MRI5/ Post	FU1/2	FU3
Vocabulary test		X							
Dot Probe Task with Alcohol stimuli		X							
Dimensional Card Sorting Task		X							
MRI	S01	MRI 1/ Baseline		MRI 2	MRI 3	MRI 4	MRI5/Post	FU1/2	FU3
Anatomical image (MPRAGE)		X		X	X	X	X		
Stop Signal Task (SST)		X					X		
Cue-Reactivity Paradigm		X					X		
Delay Discounting		X					X		
Resting State		X		X	X	X	X		
Neurofeedback				X	X	X			
Transfer				X		X			
Craving (Visual Analog Scale) pre & post scanning				X	X	X			
Perceived control over NFB (Visual Analog Scale)				X	X	X			

S01: Screening assessment and Baseline. MRI 1: MRI scanning appointment during baseline. MRI 2–4: rtfMRI NFB scanning appointments. MRI 5: MRI scanning appointment after the rtfMRI NFB sessions. FU 1–2: monthly follow-ups via telephone. FU 3: catamnestic interview (face-to-face)

### MBRP description

The MBRP training consists of five sessions, which are based on the Mindfulness-Based Relapse Prevention for Addictive Behaviors by [7]. The first session begins with a Raisin Meditation followed by a hand-out with a definition of mindfulness and explains two key concepts of mindfulness: the first one being the instruction not to judge and the second concept being the introduction of mindfulness as an alternative strategy to the mode of the autopilot. Acting on autopilot means experiencing the automatic behavior we experience during everyday life, which describes a condition of acting without conscious self-control or awareness. By stopping and observing, participants are sensitized to their thoughts and feelings. At the end of the first session the patients receive homework in form of a sheet of paper, in which they are instructed to write down time, date, feelings thoughts and behavioral impulses whenever they feel craving. The next session begins with a Body Scan Meditation. Then, difficulties during meditation are discussed and the participants are handed a worksheet which explains the concept of acceptance. The third session starts with Mindful Breathing Meditation. Furthermore, risk situations for relapse are examined and the SOBER Breathing Exercise is introduced. The participants are advised to practice the latter at least 5 minutes per day in order to be able to use this technique in risk situations which involve heavy craving. Upon a rehearsal of the SOBER Breathing training, the fourth session focuses on further examination of risk factors and a mindful way to deal with the latter. In the last session, which, as before, starts with SOBER Breathing, the homework sheet from the first session is examined. Participants receive a handout in which they are instructed to fill out answers relating to the importance of mindfulness. The session ends with a Completion Meditation. After the last session, participants who took part in the MBRP are asked to answer the Mindfulness-Based Relapse Prevention Adherence and Competence Scale [7].

### Neurofeedback setup

rtfMRI NFB is executed at a Siemens 3 T Scanner (Siemens Healthineers, Erlangen, Germany) at the Central Institute of Mental Health in Mannheim, Germany. rtfMRI NFB is delivered on three separate training days within 2 weeks. A T1-weighted anatomical MPRAGE scan, a functional resting state scan and three neurofeedback runs are performed during each session. For the EPIs we will use state-of-the-art multiband sequences.

To allow for neurofeedback signal extraction, the imaging computer transfers reconstructed DICOM images to a laptop which preprocesses the data and calculates the feedback signal using in-house scripts written in MATLAB (MathWorks Inc., Sherborn, MA, USA) based on SPM12 functions (Wellcome Department of Cognitive Neurology, London, UK).

At the start of each session, the obtained anatomical image undergoes segmentation and normalization to MNI space. For warping of the masks of the target regions into subject space, the inverse deformations of the normalization are used. During the rtfMRI NFB procedure, functional images are pre-processed with realignment and re-slicing. In a next step, the mask is adjusted to the latest image acquired and mean intensity values from the voxels in the target regions are derived. At each time step the whole available signal is corrected for nuisance effects. For display of the NFB signal, intensity values acquired in the presence of alcohol images are averaged over the last 3 volumes to allow for a stabilization of the feedback signal. Percent signal change in relation to the previous fixation cross is calculated and adapted to the maximum absolute signal change. The calculated signal is then sent to a presentation computer with Presentation software (Neurobehavioral Systems, Inc., Albana, CA, USA) where it is implemented as a thermometer value besides photos of the alcoholic drink of choice of the participant (beer, wine or schnapps) shown in randomized order (see Fig. 2). Update of the thermometer display takes place after every acquired volume.

**Fig. 2 Fig2:**
[figure not shown]
rtfMRI Neurofeedback Setup. The scanner computer reconstructs the obtained images and sends them to a laptop with in-house MATLAB scripts for preprocessing and extraction of the neurofeedback signal. The feedback value calculated is then forwarded to a computer with Presentation software and displayed as a thermometer value. The rights to this figure are reserved by the authors

### Task design

The NFB sessions follow a block design in which a fixation cross and an image of an alcoholic beverage of choice are presented alternately. 10 s after the onset of the alcoholic beverages, a feedback thermometer appears on the screen which is updated every TR (Fig. 3). After two runs of NFB, a transfer run without the feedback component follows (Fig. 4), except for the second training session in which all runs are NFB runs.

**Fig. 3 Fig3:**
[figure not shown]
Experimental Design Neurofeedback. a) A fixation cross is presented to the participant in the scanner which is followed by an image of the preferred alcoholic beverage (beer or wine) alongside a thermometer to the left and right. The thermometer value displayed is updated every TR to represent the latest value. The rights to this figure are reserved by the authors

**Fig. 4 Fig4:**
[figure not shown]
Experimental Design Transfer Run. During the transfer run no feedback is shown to the participant and the instruction is to apply the same strategies as in Fig. 3. The rights to this figure are reserved by the authors

A visual craving scale is used to evaluate the participant’s craving before and after the scanning. Additionally, participants fill in questionnaires (see Table 1).

Before the NFB starts, participants of the MBT group are reminded of their MBT training and are asked to apply the strategies they learned in the sessions. The TAU group receives sham instructions.

### Follow-up assessments

The follow-up assessments are conducted monthly, beginning after the last rtfMRI session. In total, participants are followed-up over a period of 3 months. During the first two follow-ups, participants are contacted via phone and asked whether they use any medication related to alcohol dependence. Additionally, they are inquired about their use of drugs and a possible alcohol relapse. During the last follow-up, which takes place at the CIMH 3 months after the last rtfMRI session, participants are requested to fill out alcohol-related questionnaires and are asked about substance use. For the catamnestic interview, participants are entitled to receive a monetary compensation.

### Statistical analyses

Offline analyses are conducted with SPM (Wellcome Department of Cognitive Neurology, London, UK) in MATLAB (MathWorks Inc., Sherborn, MA, USA) and include slice-time correction, realignment, segmentation of the anatomical image, normalization to MNI space and smoothing. In our first level analyses, we convolve the time courses with the canonical hemodynamic response function and add them to the General Linear Model (GLM) which also includes 6 movement parameters. The second level analyses comprise correlations with clinical variables and potentially predictive markers for the future course of the disease.

Missing data will be excluded from the analyses. Physiological activity (cardiac and respiratory) will also be recorded and then included in the first level to correct for noise of physiological nature. This will be performed via Global Signal Regression (GSR) and model-based physiology correction [52].

Clinically, the primary outcomes include the number of relapses and the number of days until relapse during the 3-months follow-up. From a neural perspective, the increase of the ability to voluntarily modulate brain activation to alcohol cues after training in the VS serves as a secondary outcome, whereas craving measures such as the Alcohol Abstinence Self-Efficacy Scale [18] will be analyzed as a primary outcome. Another secondary outcome is the influence of combined MBRP and rtfMRI NFB training on functional changes in brain networks of cognitive control (Stop Signal Task (SST), delay discounting).

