## Method

### Hypotheses

We will assess whether intervention success is associated with specific neural correlates and behavioral predictors of variable domains. A prior study has shown that patients who, preceding the intervention, are most responsive to VS cue-reactivity benefit most from the treatment [37]. Therefore, we assume that our study will show similar effects by discriminating between high- and low-responders being premised on their baseline VS cue-reactivity. We expect that the group receiving the combination treatment (real rtfMRI and MBRP) will profit most in terms of the outcome. Considering that relapse will not be defined as an exclusion criterion, we assume a decreased amount of heavy drinking days and a decreased sum of alcohol consumption. Additionally, it is assumed that the number of days until relapse will increase. In contrast to the TAU and sham NFB group, we expect that the other two groups will gain more of an advantage. As a secondary effect, we expect participants with a lower score on alcohol related questionnaires to show a superior long-term outcome in terms of a higher number of non-drinking days.

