### Sample size, group assignment and recruitment

In order to investigate a possible increased ability of our participants to deliberately reduce VS cue-reactivity through the help of MBRP, we will include *N* = 88 participants. These participants will be recruited from inpatients and outpatients of the clinics of the Department of Addiction Behavior and Addiction Medicine at the Central Institute of Mental Health (CIMH) Mannheim, Germany. After inclusion, they will be randomly assigned to four interventional groups (Fig. 1). While all groups will receive rtfMRI NFB from different brain regions, not all groups will be assigned to take part in the mindfulness-based treatment. Two groups will receive treatment as usual (TAU), whereas the other two groups receive MBRP. These two groups (TAU and MBT) will further each be divided in two subgroups, who receive either rtfMRI NFB from the VS with the instruction to down-regulate it (experimental group) or they receive feedback from the control region which is the auditory cortex (control group). The latter area was chosen since it is unrelated to cue-reactivity.

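### Read as written, the rule to exclude missing data drops unreached patients from the primary outcomes and puts the relapse comparison at risk of bias

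*Protocol article*

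**What the plan says.** All references are to the Protocol article.

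- **Missing data.** Statistical analyses states: "Missing data will be excluded from the analyses". No outcome, data type or analysis is singled out. The rest of that paragraph deals with correcting the imaging data for cardiac and respiratory noise.
- **Primary outcomes.** The next paragraph says "the primary outcomes include the number of relapses and the number of days until relapse during the 3-months follow-up", and adds that "craving measures such as the Alcohol Abstinence Self-Efficacy Scale [18] will be analyzed as a primary outcome".
- **How relapse is learned.** According to Follow-up assessments, the first two follow-ups are telephone calls: "Additionally, they are inquired about their use of drugs and a possible alcohol relapse". The third is a visit on site: "During the last follow-up, which takes place at the CIMH 3 months after the last rtfMRI session". In Table 1 the AASE and the craving questionnaires (OCDS, AUQ, CASA) appear at baseline and again only at FU3.
- **Relapsed patients.** Hypotheses says that "relapse will not be defined as an exclusion criterion".
- **Blinding.** Under Sample size, group assignment and recruitment, neurofeedback allocation is double-blind, but patients know whether they receive MBRP.

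The article gives no dropout rate. It also names no other handling of missing relapse or questionnaire data that would offset the exclusion rule.

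**The concern.** This is a stated method, not a detail left to an analysis plan. A plan that followed the sentence literally would run a complete-case analysis of the primary outcomes.

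Three things are at stake:

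- **Randomised patients are lost.** A patient who is not reached has no relapse datum, and a patient who misses FU3 has no AASE after baseline. Excluding them means the groups compared are no longer the groups randomised.
- **Observed time may be lost.** A patient reached at FU1 and FU2 but not at FU3 has about two months of known status. The sentence does not say whether only the missing value is dropped or the patient with it.
- **Missingness may depend on the outcome.** It is plausible that someone who has relapsed is harder to reach. If so, observed relapse rates are too low. If this happens more in one arm than in the other, part of the observed difference is an artefact. Patients know their MBRP status, so loss that differs between MBRP and TAU is a realistic possibility.

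**Working it through.** The article gives no figure for loss to follow-up, so there is no figure of its own to reproduce. The check is therefore an illustration, with its assumptions marked.

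**Inputs**
- True relapse by 3 months, p = 50% in both arms (assumed). Background gives only a 1-year range of 45–75%.
- Share of non-relapsers lost, mN = 10% in both arms (assumed).
- Share of relapsers lost, mR = 10% to 50% (assumed).
- N = 88 in four groups, from the article. Equal allocation is assumed, giving 88/4 = 22 per group and 88/2 = 44 for MBRP v TAU.

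**Formula.** Complete-case relapse rate = p(1 − mR) / [p(1 − mR) + (1 − p)(1 − mN)].

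**Worked cases**
- mR = 30%: 0.5 × 0.70 / (0.35 + 0.45) = 0.35/0.80 = 43.8%.
- mR = 15%: 0.5 × 0.85 / (0.425 + 0.45) = 0.425/0.875 = 48.6%.
- mR = 40%: 0.30 / (0.30 + 0.45) = 40.0%.
- mR = 50%: 0.25 / (0.25 + 0.45) = 35.7%.
- mR = 10%: 0.45 / (0.45 + 0.45) = 50.0%.

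| Relapsers lost, arm A | Relapsers lost, arm B | Rate A | Rate B | Spurious difference (points) |
|---|---|---|---|---|
| 30% | 30% | 43.8% | 43.8% | 0 |
| 40% | 40% | 40.0% | 40.0% | 0 |
| 30% | 15% | 43.8% | 48.6% | 4.8 |
| 30% | 10% | 43.8% | 50.0% | 6.3 |
| 40% | 10% | 40.0% | 50.0% | 10.0 |
| 50% | 10% | 35.7% | 50.0% | 14.3 |

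**Sensitivity to p** (30% v 15% of relapsers lost)
- p = 45%: 0.315/0.810 = 38.9% v 0.3825/0.8775 = 43.6%, a difference of 4.7 points.
- p = 75%: 0.525/0.750 = 70.0% v 0.6375/0.8625 = 73.9%, a difference of 3.9 points.

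**Effect on the test.** A two-proportion z test at a nominal 5% was simulated with no true difference. With 30/40/50% of relapsers lost in one arm and 10% in the other, the false-positive rate was 8.5/13.7/22.6% at 44 v 44 and 6.9/9.4/13.6% at 22 v 22. With equal loss in both arms it stayed at about 5%.

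**Equal loss when a true difference exists.** With true rates of 60% v 40%, and 30% of relapsers and 10% of non-relapsers lost in each arm:
- Observed rates are 0.42/0.78 = 53.8% and 0.28/0.82 = 34.1%, a difference of 19.7 points against a true 20.
- The odds ratio stays at 2.25, because each arm's odds are multiplied by the same factor, 0.70/0.90.

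**Counting every lost patient as relapsed**
- In the table's scenarios each arm gives 1 − 0.5 × 0.90 = 55%, so no spurious difference arises. This is only because non-relapsers are lost equally.
- If relapsers are lost 10% in both arms but non-relapsers 10% v 25%, the rule gives 1 − 0.45 = 55% v 1 − 0.375 = 62.5%, a spurious 7.5 points.
- Complete-case analysis then gives 0.45/0.90 = 50% v 0.45/0.825 = 54.5%, a spurious 4.5 points. The rule can therefore be worse than the method it replaces.

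**The case against.** The strongest reply is that the sentence may not mean what it seems to. It opens a paragraph on imaging noise, and it speaks of missing data, not of patients with missing data. Dropping missing values is compatible with using every observed value and with censoring at last contact. This stands in part: the reach to clinical outcomes is the natural reading, not a certain one. But the sentence is unrestricted, sits under the general analysis heading, and is the only missing-data rule given for the primary outcomes. If imaging alone was meant, the wording still has to change.

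Several stronger readings are tempting, but the documents do not support them:

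- **That the rule removes precisely the relapsed patients, or that the comparison is biased.** The article gives no dropout rate and no link between loss and relapse. With equal loss across arms, the null comparison is not biased.
- **That the rule contradicts Hypotheses.** The statement that "relapse will not be defined as an exclusion criterion" concerns a relapse that is known. A relapsed patient with data stays in, and a patient without data is unobserved. Both statements can hold.
- **That patients who never relapse are dropped.** Someone followed for the full 3 months without relapse has no missing data.
- **That power for the neural outcome falls through relapse-related loss at follow-up.** The neural outcome is secondary, and in Table 1 all five MRI sessions precede follow-up.

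The risk of differential loss also has limits. A relapse reported at FU1 is already known, the FU3 interview is compensated, and the follow-up schedule is the same for all groups. Because neurofeedback allocation is double-blind, knowledge of arm does not explain differential loss between real and sham feedback. The argument applies to MBRP v TAU.

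**Conclusion.** The concern holds as a risk created by a stated rule, not as a demonstrated bias. Taken literally, the rule analyses the primary outcomes only in patients who were reached, and it may discard observed follow-up.

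Two conditions govern the harm. If relapsers are lost more often than non-relapsers, relapse rates are understated, for example 50% observed as 43.8%. If that excess loss also differs by arm, the comparison is biased, and the direction depends on which arm loses more. In the assumed scenarios the spurious difference runs from 4.8 points (30% v 15% of relapsers lost) to 14.3 points (50% v 10%), and it is zero when loss is equal. These sizes rest on assumed loss rates, an assumed 3-month relapse rate and, for the false-positive rates, an equal split of the 88 patients.

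**What to change.** Replace the sentence with rules by outcome:

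- **Imaging:** limit exclusion to unusable MRI data, and report the amount excluded by arm.
- **Population:** analyse all randomised patients in the group assigned.
- **Days until relapse:** analyse as time-to-event, with censoring at last contact.
- **AASE/craving:** use a likelihood-based mixed model on all available observations (baseline and FU3).
- **Relapse by 3 months:** use multiple imputation. Counting missing patients as relapsed should be a sensitivity analysis only, because it adds bias of its own when non-relapsers are lost unequally.

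The cost is analysis-plan wording and modest programming, with no new data. These methods assume that data are missing at random and that censoring is uninformative given what was observed, which the sensitivity analysis probes. Two limits remain. A patient with no follow-up contact contributes no time under censoring and is covered only by imputation and the sensitivity analysis. A patient with only a baseline AASE adds little information on change. The change should be made before allocation is unblinded.

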**Methods/design:**

After inclusion, *N* = 88 patients will be randomly assigned to one of four groups. Two of those groups will receive mindfulness-based relapse prevention. All groups will receive two fMRI sessions and three real-time neurofeedback sessions in a double-blind manner and will regulate either the ventral striatum or the auditory cortex as a control region. Two groups will additionally receive five sessions of mindfulness-based relapse prevention prior to the neurofeedback intervention. After the last fMRI session, the participants will be followed-up monthly for a period of 3 months for an assessment of the relapse rate and clinical effects of the intervention.

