### Power calculations

In order to conduct our effect size calculation two studies were used: Hartwell et al. [28], with an effect size of f = .59 in a study focusing on the anterior cingulate cortex in smokers and Kirsch et al. [39], which investigated heavy social drinkers with an effect size of f = .54 for VS cue-reactivity. Additionally, we examined a study by Tang, Tang, & Posner [50] with an effect size of f = .475 on activation in prefrontal control structures after a mindfulness-based intervention. Since the above-mentioned effect sizes originate from small samples, they might be an overestimation of real effect sizes [9]. Thus, we carefully assume an intermediate effect size of f = .3. We conducted the sample size estimation by means of the G*Power software tool version 3 [19]. The region of interest (VS, 200 voxels) was amended for multiple testing based on Bonferroni correction. As a result of this effect size, we require a sample size of 88 participants to attain a significant effect at *p* < .05 (Bonferroni corrected for multiple testing, region of interest mask of 500 voxels) with a power of 80%. With this sample size of 88 participants, we will be able to identify small effects of f = .15 for our primary clinical outcomes with a power of 95% (group by time interaction).

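### Days until relapse is a primary outcome, but the article gives abstinent patients no value on it, and its exclusion rule and power statement do not fit such an outcome

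*Protocol article*

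**What the plan says.** The Statistical analyses section names two relapse outcomes as primary: "Clinically, the primary outcomes include the number of relapses and the number of days until relapse during the 3-months follow-up". It also treats craving measures as primary, with the Alcohol Abstinence Self-Efficacy Scale as the example. The Hypotheses section gives the expected direction: "Additionally, it is assumed that the number of days until relapse will increase". The window is fixed in Follow-up assessments: "In total, participants are followed-up over a period of 3 months".

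On absent values, Statistical analyses has one sentence: "Missing data will be excluded from the analyses". It makes no exception, and it stands in the paragraph before the clinical outcomes, next to text on imaging noise.

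The section names no test for the relapse outcomes. The only analysis form attached to them is in Power calculations: "we will be able to identify small effects of f = .15 for our primary clinical outcomes with a power of 95% (group by time interaction").

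**The concern.** A count of days to an event inside a fixed window is undefined for a patient in whom the event does not occur. Take three patients with complete follow-up. One relapses on day 20 and scores 20. One relapses on day 85 and scores 85. One is abstinent for all 90 days and has no score. The third has the best result, and the article does not say how that patient enters the comparison.

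What the article does fix points the wrong way. A blanket exclusion rule, applied literally, would leave a comparison among relapsers only. That conditions on a post-randomisation event and removes more patients from the better arm. The stated power form does not help, because it has no place for a censored time. The article also announces that interim analyses will be shown at conferences, so an open choice between a valid and a nearly powerless analysis could be settled after data have been seen.

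**Working it through.** **1. The article's own power figures.** For a within-between interaction in repeated-measures ANOVA, λ = f²·N·m/(1−ρ), df1 = (k−1)(m−1), df2 = (N−k)(m−1), with k groups, m time points and correlation ρ.

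- Sample size. Inputs from Power calculations: "Thus, we carefully assume an intermediate effect size of f = .3", and "Bonferroni corrected for multiple testing, region of interest mask of 500 voxels) with a power of 80" per cent. With α = 0.05/500 = 0.0001, and k = 4, m = 2, ρ = 0.5 (assumed; ρ is the software default), λ = 0.09·88·2/0.5 = 31.68 and power is 0.813. The smallest N is 87, which becomes 88 in four equal groups. The figure of 88 reproduces.
- Primary clinical outcomes. With f = .15, α = 0.05 (assumed) and the same settings, λ = 0.0225·88·2/0.5 = 7.92 and power is 0.627, not 0.95. About 95% needs other, unstated settings, for example k = 2, m = 2, ρ = 0.7 (0.949) or k = 4, m = 4, ρ = 0.7 (0.966).
- Whatever the settings, days until relapse gives one value per patient, so m = 1 and df1 = (k−1)·0 = 0. The interaction does not exist for this outcome.

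**2. Inputs for the literal reading.** From the article: 3 months of follow-up (taken as 90 days) and 88 patients in four groups. The allocation ratio is not stated; equal groups are assumed, giving 44 v 44 for one factor of the 2×2. The article gives no 3-month relapse rate and no hazard ratio (HR). Its only rate is 45-75% at one year (Background). Carried back at a constant hazard, 1 − (1 − p)^(90/365) gives 0.137 and 0.290. Early relapse may be more frequent, so 45%, 60% and 75% by day 90 are shown too.

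**3. Formulas.** With constant hazard h and T = 90:
- mean days among relapsers = 1/h − T·e^(−hT)/(1 − e^(−hT));
- restricted mean relapse-free days over all patients = (1 − e^(−hT))/h.

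**4. Worked case: 50% control relapse, HR 0.5.** Control: h = ln 2/90, so 1/h = 129.8. The relapsers' mean is 129.8 − 90 = 39.8 and the restricted mean is 0.5·129.8 = 64.9. Treated: relapse is 1 − 0.5^0.5 = 0.293 and 1/h = 259.7. The relapsers' mean is 259.7 − 90·0.707/0.293 = 42.4 (from unrounded values) and the restricted mean is 0.293·259.7 = 76.1. The gain is 11.1 days over all patients but 2.6 days among relapsers, so 77% is lost. Patients left out: 44·0.5 + 44·0.707 = 53 of 88.

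**5. Range at HR 0.5, 44 v 44, two-sided 0.05** (power from 2,000 simulated trials per row):

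| Control relapse by day 90 | Left out of 88 | Gain, all patients (days) | Gain, relapsers only (days) | Log-rank power | Relapsers-only t-test power |
|---|---|---|---|---|---|
| 14% | 79 | 3.1 | 0.6 | 0.16 | 0.04 |
| 29% | 68 | 6.5 | 1.3 | 0.33 | 0.05 |
| 45% | 57 | 10.1 | 2.2 | 0.47 | 0.05 |
| 60% | 45 | 13.3 | 3.4 | 0.59 | 0.06 |
| 75% | 33 | 16.2 | 4.9 | 0.74 | 0.12 |

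**6. Sensitivity.** Over HR 0.3, 0.5 and 0.7 and the same relapse rates, relapsers-only keeps 18-33% of the true gain, so 67-82% is lost. With an early-peaking hazard (Weibull shape 0.6, HR 0.5, 45-75% relapse) it keeps 18-25%.

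**The case against.** A reader might infer that the plan discards its treatment successes. The article does not say so. A patient seen at the last visit and found abstinent is fully observed; in ordinary usage that time is censored, not missing. The exclusion sentence stands among imaging text, and the hypothesis that days until relapse will rise sits badly with removing the longest abstainers. That dropping them is planned is therefore a literal reading, not a stated intention.

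The power sentence likewise does not show that an ANOVA among relapsers is planned. It suits a repeated measure such as the self-efficacy scale, which Table 1 schedules at baseline and at the third follow-up. A censoring rule and a named survival model are also things that an article commonly leaves to the full protocol or the SAP.

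All of this stands, and it limits the point. It does not remove it. Silence about censoring alone would be no finding, but the article goes further: it writes an exclusion rule without exception, and it claims 95% power for the primary clinical outcomes in a form that one of them cannot take.

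**Conclusion.** The point holds as a defect of wording in one primary outcome. The article fixes days until relapse as primary, leaves it undefined for abstainers, and surrounds it with an exclusion rule and a power statement that do not fit it. If the rule were applied literally, about 67-82% of the difference in relapse-free days would be lost. At HR 0.5 and 44 v 44, power would be about 4-12%, against 16-74% for a log-rank test. These sizes rest on assumed proportional hazards, an assumed HR and an assumed 90-day relapse rate. The loss would be smaller if treatment mainly delayed relapse within the 90 days.

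A reader might go on to conclude that an effective treatment would be reported as having no effect. The documents do not support that. The number of relapses is also primary and keeps abstainers at zero. And at the 14-29% relapse derived from the article's one-year rates, a log-rank test itself has only 16-33% power at HR 0.5, so a non-significant result could not be put down to the exclusion rule alone.

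**What to change.** In Statistical analyses:

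- Define the outcome as time to first relapse. Censor patients without relapse at their last drinking assessment, which is the third follow-up if follow-up is complete.
- Limit the exclusion rule to data that were not observed, and say that absence of relapse is not missing data.
- Compare the randomised groups by a log-rank test or a Cox model with NFB region, MBRP and their interaction, or by restricted mean relapse-free days to the end of follow-up.

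In Power calculations, limit the f = .15, 95% power statement to outcomes measured repeatedly, and do not claim it for days until relapse.

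The cost is wording only. Table 1 already schedules drinking interviews at all three follow-ups, so no new data are needed.
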